## Abstract

**Aims:**

In acute myocardial infarction (AMI), impaired myocardial salvage and large infarct size result in residual heart failure, which is one of the most important predictors of morbidity and mortality after AMI. Sleep-disordered breathing (SDB) is associated with reduced myocardial salvage index (MSI) within the first 3 months after AMI. Adaptive servo-ventilation (ASV) can effectively treat both types of SDB (central and obstructive sleep apnoea). The Treatment of sleep apnoea Early After Myocardial infarction with Adaptive Servo-Ventilation trial (TEAM-ASV I) will investigate the effects of ASV therapy, added to percutaneous coronary intervention (PCI) and optimal medical management of AMI, on myocardial salvage after AMI.

**Methods/design:**

TEAM ASV-I is a multicentre, randomised, parallel-group, open-label trial with blinded assessment of PCI outcomes. Patients with first AMI and successful PCI within 24 h after symptom onset and SDB (apnoea–hypopnoea index ≥ 15/h) will be randomised (1:1 ratio) to PCI and optimal medical therapy alone (control) or plus ASV (with stratification of randomisation by infarct location; left anterior descending (LAD) or no LAD lesion). The primary outcome is the MSI, assessed by cardiac magnetic resonance imaging. Key secondary outcomes are change of infarct size, left ventricular ejection fraction and B-type natriuretic peptide levels and disease-specific symptom burden at 12 weeks.

**Conclusion:**

TEAM ASV-I will help to determine whether treatment of SDB with ASV in the acute phase after myocardial infarction contributes to more myocardial salvage and healing.

**Trial registration:**

ClinicalTrials.gov, NCT02093377. Registered on March 21, 2014.

## Background

After acute myocardial infarction (AMI), myocardial salvage is central to limiting permanent damage to the heart because large infarct sizes result in enduring heart failure (HF) [1], which is the most important predictor of morbidity and mortality after AMI [2]. Infarct expansion is promoted by intermittent hypoxia [3, 4] and left ventricular mural pressure [1]. Both intermittent hypoxia and increased left ventricular mural pressure are hallmarks of sleep-disordered breathing (SDB) [5]. Therefore, patients with AMI may be highly sensitive to the deleterious effects of SDB [6].

Recent observational studies suggest that at least a moderate degree of SDB affects up to 66% of patients in the early phase after AMI [6, 7]. Patients with AMI are affected by two main types of SDB: obstructive sleep apnoea (OSA) and central sleep apnoea (CSA) [6, 8]. OSA is characterised by repetitive collapses of the upper airway during sleep and continued respiratory effort during apnoeas. Inspiratory efforts against the occluded pharynx during obstructive apnoeas generate exaggerated negative intrathoracic pressure that increases left ventricular transmural pressure and, as a result, afterload [5]. Additional acute consequences of OSA include repetitive oxygen desaturations, sympathetic nervous system activation, increased heart rate and elevated blood pressure [5, 9]. In contrast to OSA, there is no upper airway obstruction and no respiratory effort during central apnoeas [10]. CSA in patients with impaired cardiac function typically shows a characteristic periodic breathing pattern with a waxing and waning of tidal volume (Cheyne Stokes respiration) [10]. Similar to OSA, CSA causes intermittent nocturnal hypoxia, arousals from sleep, repetitive sympathetic nervous system activation, and swings in heart rate and blood pressure, but does not generate negative intrathoracic pressures [10].

Especially in the early phase after AMI, SDB is associated with increased cardiac workload [11], prolonged myocardial ischaemia [12], increased infarct size and reduced myocardial salvage index within the first 3 months [13]. Other negative consequences of SDB in this setting have been reported, such as worse left ventricular ejection fraction (LVEF) [14], enlargement of the right heart [15] and disturbed cardiac repolarisation [16]. All of these unfavourable aspects of SDB impair myocardial salvage after AMI, contributing to the development of HF. In addition, SDB per se promotes the development and progression of HF [10], making SDB a worthwhile target of therapy to prevent, or at least alleviate, HF development after AMI.

Previous randomised controlled trials in patients with AMI and SDB evaluated the effects of continuous positive airway pressure (CPAP) on major cardiovascular events [17, 18]. Both studies did not find a significant effect of CPAP on major cardiovascular events [17, 18]. In contrast to the present proposed study, TEAM-ASV I, cardiac magnetic resonance imaging (CMR) was not performed and myocardial salvage index was not studied [17, 18]. In a systematic review no other randomised controlled trials evaluating the effects of positive airway pressure therapy on myocardial salvage index using CMR could be identified.

Adaptive servo-ventilation (ASV) is currently the most effective therapy with respect to normalisation of nocturnal breathing in patients with impaired cardiac function plus CSA and OSA, with or without periodic breathing [19]. However, the effects of nocturnal ASV therapy on myocardial salvage, infarct mass and size and left ventricular function in patients with AMI and SDB have not been studied to date. Treatment of SDB in the early phase after AMI may constitute a new therapeutic opportunity to prevent development of HF after AMI. Considering the therapeutic equipoise of treatment of SDB in the early phase after AMI, a randomised controlled trial is justified. Therefore, the Treatment of SDB early After Myocardial infarction with Adaptive Servo-Ventilation trial (TEAM-ASV I) was designed to test the effect of ASV therapy, added to percutaneous coronary intervention (PCI) and optimal medical management, on myocardial salvage after AMI.

## Methods/design

### Study design

TEAM ASV I is a multicentre, randomised, parallel group, open-label trial with blinded assessment of outcomes. It will compare treatment with PCI and optimal medical therapy (control group) with PCI, optimal medical therapy and ASV (ASV group) in patients with AMI and SDB. The trial is an investigator-initiated and run study, funded by the ResMed Foundation (La Jolla, CA, USA); ResMed Germany (Martinsried, Germany) is providing the ASV devices. The trial was approved by the relevant institutional ethics committee (Ethikkommission der Universität Regensburg, approval number 11–101-0229) and is being conducted in accordance with the Declaration of Helsinki. All patients will provide written informed consent before undergoing study investigations. This trial has been registered with ClinicalTrials.gov (www.clinicaltrials.gov; NCT02093377).

The trial began enrolment in March 2014 and is expected to end enrolment in December 2020. As of writing, a total of 67 of the 90 target patients have been randomized.

### Study oversight

The study is monitored by an independent data safety monitoring committee (DSMC), comprising three clinical trial experts (two cardiologists and an independent statistician) who will review serious and non-serious adverse events throughout the study. An interim safety analysis is pre-specified after randomisation of the 35th patient and will include all safety variables related to this trial (study device-related and non-related events).

### Study population

Consecutive patients with their first AMI in a stable haemodynamic condition will be assessed for eligibility according to the inclusion and exclusion criteria shown in Table 1. After providing written informed consent, further evaluation of eligibility will follow, including medical history, physical examination and SDB assessment using cardiorespiratory polygraphy. The study has no gender-based selection criteria. In accordance with the epidemiology of AMI and SDB, the majority of participants (80–90%) are expected to be male [6].

**Table 1 Tab1:** Inclusion and exclusion criteria

Inclusion criteria	
- Aged 18–80 years - First AMI - ST elevation in ECG or acute occlusion of coronary artery - Primarily successful PCI achieved < 24 h after onset of symptoms - SDB (apnoea-hypopnoea index ≥ 15/h of total recording time) - Written informed consent	
Exclusion criteria	
- Previous myocardial infarction - Previous myocardial revascularisation (PCI or surgical) - Indication for surgical revascularisation - Cardiogenic shock - Mean supine blood pressure < 60 mmHg - NYHA class IV - Implanted cardiac device or other contraindications for CMR - Known allergies or a contraindication to contrast dye (e.g. GFR < 30 mL/min/1.73m^2^) - History of stroke - Contraindications for positive airway pressure support (mean supine blood pressure < 60 mmHg, inability to clear secretions, risk of aspiration of gastric contents, history of pneumothorax and/or pneumomediastinum, a history of epistaxis causing pulmonary aspiration of blood) - Severe obstructive or restrictive airway disease - Heart failure due to primary valve disease - Patients on, or with indication for, oxygen therapy - Mechanical ventilation - Non-invasive ventilation - Nocturnal positive airway pressure support - Diurnal symptoms of OSA requiring immediate treatment - Awaiting heart transplantation - Pregnancy	

*AMI* acute myocardial infarction, *CMR* cardiac magnetic resonance imaging, *ECG* electrocardiogram, *GFR* glomerular filtration rate, *NYHA* New York Heart Association, *OSA* obstructive sleep apnoea, *PCI* percutaneous coronary intervention

### Randomisation

Randomisation will be performed by using the online randomization tool Randomizer (https://www.randomizer.at/) supervised by the Center of Clinical Studies. This tool ensures a secret randomization schedule for all participants and offers a 24/7 online randomization service. Randomisation to the intervention arms will be performed in a 1:1 ratio and will be stratified for infarct location (e.g. left anterior descending artery (LAD) lesion and no LAD lesion) and study site. In addition to PCI, patients randomised to the control group receive optimal medical therapy for the management of AMI according to current guidelines [20, 21]. Patients randomised to the ASV group receive optimal medical therapy for the management of AMI according to current guidelines [20, 21] plus treatment of SDB with ASV (AutoSet™ CS –Pace Wave, ResMed Corp., San Diego, CA, USA).

### Intervention: adaptive servoventilation

Following baseline assessments, patients randomised to ASV will be fitted with a comfortable nasal mask. Full face masks are only provided if the nasal mask cannot be tolerated or treatment of SDB is not possible with it (e.g. due to major mouth breathing and leakage) The patient will use the device during the daytime to achieve acclimatisation and to allow further adjustments to minimise leaks. Daytime device use will take place for 30–120 min until the patient feels comfortable with the mask and the device and leak is minimised. Night time treatment initiation will be performed under polygraphic monitoring. Default device settings include autotitrating expiratory positive airway pressure (EPAP) of 5–15 cmH_2_O with adaptive inspiratory pressure support of 0–15 cmH_2_O. Further pressure adjustments and the use of heated humidification is at the discretion of the investigator. Standardised recommendations are provided. Device usage for at least 6 h every night is recommended.

### Baseline assessments

Baseline assessments are performed in all patients meeting the inclusion and exclusion criteria. These include demographics, medical history, physical examination, ECG, cardiac magnetic resonance imaging (CMR), laboratory testing and completion of the Seattle Angina Questionnaire within 5 days after PCI (in-patient) (Fig. 1).

**Fig. 1 Fig1:**
[figure not shown]
Schedule of study visits. *ASV* adaptive servo-ventilation, *ECG* electrocardiogram, *OMT* optimal medical therapy, *SAQ* Seattle Angina Questionnaire

### Follow-up

Follow-up visits are performed after 2, 4 and 12 weeks to assess outcome measures and adverse events and to ensure compliance with the allocated treatment. Details of assessments at each visit are provided in Fig. 1. Changes of medical therapy are documented in both groups (control and ASV). In the ASV group at all follow-up visits, ASV-device data, including usage, mask leak, respiratory data and applied pressures, are collected to ensure effective therapy and compliance.

### Objectives

The primary objective is to evaluate the effects of 3 months of ASV therapy in addition to PCI and optimal medical management of AMI on myocardial salvage (myocardial salvage index (MSI)), assessed by CMR. Secondary objectives are listed in Tables 2 and 3.

**Table 2 Tab2:** Secondary objectives

Secondary objectives	
To determine the effects of 12 weeks’ ASV in patients with SDB early after AMI on the following: - Infarct size - Left ventricular remodelling assessed using CMR (myocardial salvage, microvascular obstruction, change of infarct size, infarct size at 12 weeks, change in left ventricular ejection fraction, left ventricular end-systolic volume, left ventricular end-diastolic volume) - NT-proBNP levels - Disease-specific symptom burden (Seattle Angina Questionnaire) - Daytime and night time blood pressure and heart rate - Total cholesterol and low-density lipoprotein cholesterol - SDB (apnoeas and hypopnoeas per hour of sleep, mean oxygen saturation) - Renal function (GFR, calculated using the 4v-MDRD formula) - Biochemical markers of inflammation and vascular function (hsCRP, blood count, fibrinogen)	

*AMI* acute myocardial infarction, *ASV* adaptive servo-ventilation, *CMR* cardiac magnetic resonance imaging, *GFR* glomerular filtration rate, *hsCRP* high-sensitivity C reactive protein, *NT-proBNP* amino terminal-pro B-type natriuretic peptide, *SDB* sleep-disordered breathing

**Table 3 Tab3:** Cardiac magnetic resonance imaging protocol

Examinations at baseline and after 12 weeks	
Infarct size: - Myocardial oedema (area at risk) - Myocardial salvage index - Left ventricular volumes and mass - Left ventricular ejection fraction	
Technical standards	
- The salvaged myocardium is defined as area at risk minus final infarct size - The myocardial salvage index (MSI) is defined as area at risk minus final infarct size as a percentage of the area at risk - The area at risk is measured 3 to 5 days after PCI and final myocardial infarct size is measured 12 weeks later - Patients will be examined in supine position with care taken to ensure identical position in the scanner for both exams - All images will be acquired using ECG gating technique - Cine images will be acquired with a steady state free precession sequence according to a systematic protocol - The entire left ventricle is covered with a stack of short axis images - Short-axis T2w-STIR imaging is used for myocardial oedema imaging - 10–15 min after bolus injection of gadolinium contrast medium (0.2 mmol/kg body weight) myocardial DE-CMR will be performed with consecutive short axis slices - All analyses will be conducted according to established standard operating procedures - Calculation of left ventricular volumes and ejection fraction is performed using standard available analysis software - The extent of myocardial oedema and delayed enhancement in each image will be quantified with standard analysis software - Regions of infarct-related area at risk (oedema) and myocardial infarction were identified as hyperintense regions within the T2w-STIR images and DE-CMR images, respectively - The myocardium at-risk region and the infarcted region is delineated automatically with manual adjustment when needed on delayed enhancement imaging - All measurements will be expressed as percentage of the total left ventricular myocardial mass and quantified in grams	

*DE-CMR* delayed enhancement cardiac magnetic resonance imaging, *ECG* electrocardiogram, *PCI* percutaneous coronary intervention, *T2w-STIR* T2-weighted short-tau inversion recovery

### Outcomes

#### Polygraphy

Polygraphy (SOMNOscreen™ plus RC, SOMNOmedics, Randersacker, Germany) will be performed within 3 days after PCI and repeated at the 12-week follow-up visit in both treatment groups (Fig. 1). Polygraphy evaluation includes breathing parameters (such as pressure cannula, snoring, thoracic and abdominal respiratory effort measures), oxygen saturation, ECG (including estimates of systolic and diastolic blood pressure based on the pulse-transit time method using validation references), recording of body position and light detection as well as a patient marker.

All polygraphy data are analysed by a central scoring lab to ensure consistency and quality. Each centre will send three respiratory recordings to the central lab for checking and validation as part of quality control. Apnoeas and hypopnoeas will be scored according to American Academy of Sleep Medicine (AASM) 2012 criteria by one experienced sleep technician blinded to the clinical data [22]. SDB is defined as an apnoea-hypopnoea index (AHI) ≥ 15/h (based on total recording time) and is categorised as predominantly OSA (≥ 50% of apnoeas obstructive) or predominantly CSA (< 50% of apnoeas obstructive).

#### Cardiac magnetic resonance imaging protocol

Myocardial salvage, infarct size and left ventricular function will be examined in both groups using CMR at baseline and after 12 weeks of treatment. The baseline CMR is performed to visualise myocardial oedema (i.e. the area at risk) and baseline infarct size. The second CMR is performed to measure the final infarct size.

All CMR images will be acquired with a 1.5 or 3.0 Tesla clinical scanner, as previously described [13]. The scan protocol will be standardised at all sites. Patients will be examined in the supine position with care taken to ensure identical position in the scanner for both exams. All images will be acquired during breath hold and using an ECG gating technique. Cine images will be acquired with a steady-state free precession sequence in two-chamber, four-chamber and short-axis planes. Short-axis T2w-STIR will be used for myocardial oedema imaging. Infarct size will be assessed in delayed enhancement short-axis images (segmented inversion recovery SSFP technique) covering the whole ventricle, acquired 10–15 min after bolus injection of gadolinium contrast (0.2 mmol/kg body weight). Image analysis for the assessment of ejection fraction, area at risk and infarct size, total left ventricular mass and volumes using a semi-automatic approach will be performed in anonymised form by blinded operators with commercially available software. The salvaged myocardium is defined as area at risk minus final infarct size. MSI (primary endpoint) is defined as area at risk minus final infarct size as a percentage of the area at risk (Fig. 1).

#### Laboratory testing

Venous blood samples (10 mL + optional 40 mL) and urine (100 mL) will be collected from every patient participating in the study during the first 2 h after morning awakening at baseline and at 12 weeks (Fig. 1). Part of each sample (10 mL) will be used to measure levels of plasma amino terminal-pro B-type natriuretic peptide (NT-proBNP), total cholesterol, low-density lipoprotein (LDL) cholesterol, serum creatinine, high-sensitivity C-reactive protein (hsCRP), blood count and fibrinogen. The examination will be done in an assigned central laboratory.

#### Disease-specific symptom burden questionnaire

Patients will be asked to complete the Seattle Angina Questionnaire [23] at baseline and at the final visit. Baseline and follow-up data will serve to document differences between these time points rather than evaluating changes over time. This approach accounts for the difficulties of quality of life assessment soon after a life-changing event (AMI). The Seattle Angina Questionnaire assesses subjective limitations of physical and daily activities by symptoms of coronary disease. Questionnaire scoring is undertaken as described previously [23].

#### Assessment and reporting of adverse events

Deaths, recurrent AMI, recurrent PCI, coronary bypass surgery, stent thrombosis, cerebral infarction, ventricular arrhythmia, rehospitalisation for heart failure or angina pectoris, cerebral infarction, syncope and other unexpected events will be documented at any visit and at first notice throughout the entire follow-up period. The investigator must report in detail all adverse signs and symptoms which are either volunteered by patients or observed during or following the course of investigational product administration. All AEs (including serious, unexpected/unanticipated device-related AEs (UADEs)) have to be documented in the CRF and source documents. Safety analyses will be performed in the safety population including participants who will have at least one post-baseline safety assessment. Patient informed consent includes long-term follow-up phone interviews after the 3-month trial period to assess mortality at 1, 3 and 5 years after randomization.

### Statistical analysis

#### Sample size calculation

The maximum possible effect of ASV therapy on MSI would be a reduction of 25, as calculated from a previous prospective observational study (MSI in no SDB versus SDB group, 77 versus 52) [13]. We consider that the minimum clinically relevant effect would be an MSI improvement of 10 in the ASV group compared with the control group. According to Eitel et al. [2] this degree of improvement in the MSI is associated with a 0.6 times lower risk of developing a major cardiovascular event after AMI. Therefore, to detect a MSI difference of 10 with a standard deviation of 15 ^13^ with a power of 1 − β = 80%, at a two-sided alpha significance level of 0.05, the required sample size for a randomised trial is 37 patients per group (total 74 patients). With an estimated loss to follow-up rate of approximately 17% based on previous observational data, 90 randomised patients (45 per group) are required.

#### Data analysis

The point estimate for the primary endpoint (MSI) will be presented as mean and standard deviation (SD) with the corresponding 95% confidence interval (CI). MSI values will be compared between the ASV and control groups by an analysis of covariance (ANCOVA) with treatment (ASV therapy and control) as the fixed factor and infarct size at baseline, infarct location and study centre as an additional covariable. The results will be presented in terms of least-squares means and corresponding 95% CI. The primary analysis will be performed on an intention-to-treat basis (ITT analysis set, all randomised patients). In addition, we will perform a sensitivity analysis in a per-protocol analysis set (PP population) to assess the robustness of the results. The PP population consists of all patients in the ITT population who show no major protocol violations. Major and minor protocol deviations will be identified before database lock. In addition, an on-treatment analysis, including patients with positive airway pressure support use for ≥ 4 h/day and an on-treatment AHI of < 10/h, will be performed. All safety data will be analysed in the safety population (all patients who had at least one post-baseline safety assessment). Additional pre-specified subgroup analyses are: LAD versus non-LAD lesions; central versus obstructive sleep apnoea; and PCI < 24 h versus ≥ 24 h after symptom onset.

No imputation methods for missing values will be used for the analyses of the primary and secondary endpoints (complete case analysis). In case of 5 to 40% missing data regarding the primary endpoint, a multiple imputation method will be used for further sensitivity analyses. If more than 40% of the data are missing, the trial results may only be considered as hypothesis generating results [24].

All secondary endpoints will be analysed in an exploratory manner and summarised using descriptive statistics. Safety variables will be analysed descriptively. The interim analysis after randomisation of the 35th patient will include safety variables only. All efficacy analyses will be performed on the ITT population and will be two-sided at a significance level of 0.05. All statistical analyses will be performed using SAS software version 9.4 or higher.

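### The primary ANCOVA is valid but omits the baseline area at risk, the denominator of the endpoint, and so gives up precision that would cost almost nothing to keep

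*Protocol article*

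**What the plan says.** The Data analysis section of the protocol article specifies an ANCOVA with treatment as the fixed factor and "infarct size at baseline, infarct location and study centre as an additional covariable". Infarct location and study site are also the two stratification factors named under Randomisation.

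The endpoint is defined in the CMR section: "MSI (primary endpoint) is defined as area at risk minus final infarct size as a percentage of the area at risk". Table 3 places the area-at-risk measurement 3 to 5 days after PCI and the final infarct size 12 weeks later. The first scan supplies both baseline quantities: "The baseline CMR is performed to visualise myocardial oedema (i.e. the area at risk) and baseline infarct size".

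The Sample size calculation section plans "to detect a MSI difference of 10 with a standard deviation of 15" "at a two-sided alpha significance level of 0.05", with 80% power. It mentions no covariate and no variance explained.

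**The concern.** An ANCOVA gains most from a covariate that predicts the outcome well, and the baseline counterpart of the outcome is usually the first candidate. Here the outcome is salvage relative to the area at risk. Baseline infarct size alone cannot separate a large area at risk with good salvage from a small one with poor salvage. For example, a baseline infarct of 15% of LV mass corresponds to a baseline salvage of

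- 100 × (20 − 15)/20 = 25 if the area at risk is 20% of LV mass;
- 100 × (40 − 15)/40 = 62.5 if it is 40%.

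The planned model treats these two patients alike, apart from what location and centre tell it. What is at stake is the width of the confidence interval for the treatment effect in a trial of 90 patients. The validity of the comparison is not at stake.

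**Working it through.** **1. The plan's own figure.** Inputs from the Sample size calculation section: difference 10, SD 15, two-sided alpha 0.05, power 80%.

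- Normal approximation: n = 2 × (1.960 + 0.842)² × 15²/10² = 35.3, so 36 per group.
- Noncentral t: power 0.797 at 36 and 0.808 at 37, so 37 per group, as stated.
- Loss of 17%: 37/0.83 = 44.6, so 45 per group and 90 in total, as stated.

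With no covariate gain at all, power at 37 per group is 81–82%. The stated power therefore does not depend on which covariates are chosen.

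**2. Gain for an assumed baseline-to-final MSI correlation.** The article gives no such correlation, so 0.3, 0.5 and 0.7 were tried in a large simulation (400,000 patients per scenario). Other assumptions:

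- area at risk: mean 30% of LV, SD 8 or 12;
- correlation of location with area at risk: 0.5;
- correlation of baseline salvage with area at risk: 0 or −0.3;
- unadjusted SD 15, 37 per group.

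Every model contains location. With s the residual SD, the 95% CI half-width is 1.96 × s × √(2/37), and power is Φ(10/(s√(2/37)) − 1.96).

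One scenario in full (correlation 0.5, area-at-risk SD 12, no correlation of salvage with area at risk), with √(2/37) = 0.2325:

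- Planned covariates: s = 14.30; half-width 1.96 × 14.30 × 0.2325 = 6.52; power Φ(3.01 − 1.96) = 0.853.
- Area at risk added: s = 13.29; half-width 6.06; power Φ(3.24 − 1.96) = 0.899.

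Across all scenarios:

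| Correlation | Power, planned | Power, area at risk added | Power, baseline salvage index added | Half-width, planned | Half-width, area at risk added | Half-width, index added |
|---|---|---|---|---|---|---|
| 0.3 | 83–84% | 85% | 85% | 6.6–6.7 | 6.5–6.6 | 6.5 |
| 0.5 | 85–88% | 90–91% | 91% | 6.2–6.5 | 6.0–6.1 | 5.9 |
| 0.7 | 89–94% | 97% | 98% | 5.6–6.2 | 5.0–5.2 | 4.9 |

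Compared within each scenario, adding the salvage index gains 1–2, 3–6 and 4–9 power points at the three correlations. Adding area at risk captures most of this. At 0.3 the gain is slight. For example, residual SD falls from 14.54 to 14.36 with area at risk added, a variance reduction of 1 − (14.36/14.54)² = 2.5%.

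**3. Gain when final infarct size is built from the baseline scan.** Assumptions:

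- area at risk 35% of LV, SD 8 or 12;
- baseline salvage 45, SD 18;
- 20% infarct shrinkage;
- final error SD 2, 3.5 or 5% of LV;
- correlation of area at risk with salvage from −0.3 to 0.3;
- correlation of location with area at risk 0.5.

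Each scenario was run with baseline infarct size free of error and again with an error of 3% of LV, giving 36 scenarios. Residual variance fell in all of them: by about 12–69% without baseline error and about 6–45% with it.

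In a central error-free case, R² rose from 0.29 to 0.56 when the salvage index replaced baseline infarct size. Scaled to SD 15, with t(0.975, 72) = 1.993:

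- planned: 1.993 × 15 × √0.71 × 0.2325 = 5.9;
- with the index: 1.993 × 15 × √0.44 × 0.2325 = 4.6.

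This case is favourable, because it ignores baseline measurement error.

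**The case against.** The strongest reply is that this is a preference between two valid models. The plan pre-specifies an ANCOVA with a pre-treatment imaging covariate and both stratification factors, and any other prognostic covariate changes efficiency only. That stands, and the point is put no higher.

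Three stronger readings are tempting, and the article supports none of them.

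- *A reader might infer that the model adjusts for infarct size alone and discards the area-at-risk information.* Location and centre are also in the model. Infarct size itself depends partly on the area at risk, and location may carry more of that information (an assumption). Part of it is therefore already used.
- *A reader might infer that the trial is biased or underpowered as planned.* The sample size rests on the unadjusted SD of 15, and its figure reproduces. Under the assumed correlations above, the planned model already has 83–94% power. Chance imbalance in area at risk is limited by stratification on location, and what remains is reflected in the confidence interval.
- *A reader might infer that a baseline MSI is already a defined measurement, because Table 3 lists MSI under* "Examinations at baseline and after 12 weeks". That heading covers a pooled list for both visits, and MSI is defined only with the final infarct size. A baseline version can be computed from the first scan but needs its own definition.

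It is also fair to object that any large figure for the gain depends on assumptions. Baseline measurement error alone lowers the upper end of the variance reduction from 69% to 45%.

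What the objection does not remove is that every scenario tried showed some gain. The change also loses no patients, because anyone with a computable MSI has an area at risk by definition.

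**Conclusion.** The point holds as a recommendation on efficiency. The only baseline CMR covariate in the primary model is infarct size. The endpoint's denominator, known from the same scan before ASV is fitted, is left out. The planned analysis is valid and meets its stated power.

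The size of the gain cannot be settled from the article, which gives neither a baseline-to-12-week correlation nor a distribution for the area at risk. Under the stated assumptions it runs from negligible to substantial: about 1–2 power points at a correlation of 0.3, 3–6 at 0.5 and 4–9 at 0.7. In the scenarios built from scan values, residual variance falls by roughly 6–69%, or about 6–45% with baseline measurement error of 3% of LV. The lower of these two ranges is the safer guide.

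**What to change.** Choose one of two changes to the primary model:

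1. Keep baseline infarct size, infarct location and study centre, and add baseline area at risk. This needs no new definition and costs one degree of freedom.
2. Replace baseline infarct size with a baseline salvage index, defined in the text as 100 × (area at risk − baseline infarct size)/area at risk. Keep location and centre. This costs no extra degree of freedom.

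State the assumed baseline-to-12-week correlation, or say that it is unknown. Report the currently worded model as a sensitivity analysis.

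Timing matters more than wording. The trial is open-label, and 67 of the 90 patients had been randomised when the article was written. The change should therefore be fixed by a dated amendment before anyone sees outcome data by arm; a promise to settle it before database lock is a weaker safeguard. No new data are needed, and no patient drops out of the complete-case analysis.
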